### Current mood and affect

The Profile of Mood States (POMS) [28, 29] and Positive and Negative Affect Scale (PANAS) [30] will be administered to measure participants current range of feelings. The PANAS consists of 20 terms that are rated on a 5-point scale regarding how strongly they currently experience the described feeling ranging from 1 = not at all to 5 = extremely. Half of the items are added up to a positive affect score, the other half to a negative affect score [30]. The items of the POMS are rated on a 7-point scale from 1 = not at all to 7 = extremely. The questionnaire consists of 35 items, which belong to the four different subscales “*depression*”, “*fatigue*”, “*displeasure*” and “*vigor*” [28, 29].

### High-definition transcranial direct current stimulation (HD-tDCS)

We will use 4 x 1 ring electrodes for high-definition tDCS (Fig 5; Soterix Medical, NY, USA). One central electrode (anode or cathode) will be placed over the target brain region and four return electrodes will be placed around the central electrode in a ring-shape. This method is safe and well-tolerated with effective sham-control in older adults for up to 3 mA [45]. Total current density will be monitored by the device and will thus remain below safety limits [45]. For right or left inferior frontal gyrus stimulation, the central electrode will be placed over FC6 or FC5. For the right superior parietal gyrus, the central electrode will be placed over P4 according to the 10–20 system [46]. The adjoining electrodes will be placed approximately 3.5 cm away from the central electrode.

**Fig 5 pone.0289532.g005:**
[figure not shown]
Electrode montage and current flow for high-definition transcranial direct current stimulation. We will modulate the right inferior frontal lobe (FC6; A), the left inferior frontal lobe (FC5; B), or the right superior parietal lobe (P4; C). Simulation illustrates current flow through the brain. Positive values (red) indicate an increase, negative values (blue) a decrease in excitability of neurons. Simulations were created with SimNIBS (version 3.2.6) [47].

Real tDCS will consist of a 30 s ramp-up phase followed by constant current at 1 mA for 20 min and ramp-down for 30 s. For sham stimulation, the current will be ramped up to a current of 1 mA just as for real tDCS but it will be immediately ramped down again (in the beginning and at the end of 20 min). This sham procedure will produce similar sensations as real stimulation without exerting any stimulation effects [45, 48]. At the end of the experiment, side effects, and the participants’ perception of the stimulation condition will be captured [32]. We will regularly change the central electrode to prevent them from heavy and irregular abrasion [49, 50]. In addition, each set of electrodes will be used for 35 participants (i.e., each electrode will be used seven times as central and 28 times as a circle electrode). Lead quality of the electrodes will be measured after mounting of the electrodes, right before the start of the stimulation, and before demounting the electrodes. To ensure safety, the device will alarm and abort stimulation, if lead quality drops to a critical level. Should participants experience discomfort with the stimulation, it can be aborted at any point in time.

### Statistical analysis

Our primary outcome measures will be performance in attentional control and laboratory prospective memory tasks: From the ANT, we will evaluate the controlling variable. From the TAP, we will use the number of false alarms in the Go/No-Go tasks, correct answers in the flexibility task, the number of missed targets in the dual task, and mean reaction times. For laboratory prospective memory, accuracy and reaction times will be evaluated. We will use mixed ANOVAs or mixed effects models for statistical analysis of stimulation effects on primary outcome variables (depending on whether there will be any missing data). In contrast to an ANOVA, mixed effects models are better capable of handling missing data and they also allow an analysis of data on a trial level while taking hierarchical structures of data and variability within subjects into account. We will use session (first, second) as within-subject factor and condition (six experimental groups or sham) as between-subject factor. We will determine whether inhibiting or enhancing activity in the left or right frontal inferior lobe or the right superior parietal lobe will modulate attentional control or prospective memory.

As secondary outcomes, we will evaluate accuracy of the ongoing task as well as ICV of reaction times during attentional control or the ongoing-task of the laboratory prospective memory paradigm. In addition, we will test whether stimulation will have any effect on alerting or orienting (i.e., ANT Task). We will then test whether attentional control significantly predicts laboratory, naturalistic, or self-reported prospective memory using multiple linear regression.

Further we plan to model laboratory prospective memory responses by using multinomial modelling of response probabilities [51]. This approach estimates both the prospective component (i.e., remembering *that* you have to do something) and the retrospective component (e.g., remembering *when* and *what* you have to do) of prospective memory.

We will include age as a covariate in all models since it significantly influenced prospective memory in our previous study [52]. We will control for any potential influence of mood or agitation on cognition and test, in an exploratory analysis, whether mood or heart rate of participants will influence attentional control or prospective memory. Further we examine, whether one of these two measures are modulated by non-invasive brain stimulation. For an assessment of heart rate, we will include changes in beats per minute (relative to baseline) between the start of stimulation until two minutes after its end (i.e., 22 minutes). Generalized estimated equations will then be used to test any longitudinal stimulation effects on heart rate during the stimulation session [53–55].

We will use R (version 4.2.1) with RStudio (version 2022.02.3) for statistical analyses with *p* < 0.05 considered statistically significant. We will correct for multiple-comparisons using Bonferroni-Holm correction. Whenever the assumptions of normality and homogeneity are not met, data will be transformed and/or non-parametric alternatives will be used. We will only analyse data of participants that attended both sessions.

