### Randomization

A total of 105 healthy older adults will be included, stratified by age and sex. All participants will be randomly assigned to one of six experimental groups or the control condition (i.e., sham stimulation). They will receive anodal or cathodal high-definition tDCS of the right inferior frontal lobe, the left inferior frontal lobe, or the right superior parietal lobe, or sham. For sham stimulation, we will randomly place the electrodes over the same regions. Randomization will be done by JP based on a Matlab script written by TR (allocation ratio 1:5, stratified by age and sex). Neither JP nor TR will be involved in data collection. The study will follow a double-blind design, such that neither the participants nor the experimenter will be aware of the stimulation condition. Unblinding will occur at the end of data acquisition. Exceptions will only be allowed in case of adverse events.

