### Study procedure

All participants will be tested twice to differentiate learning effects from stimulation effects (Fig 2). All assessments will be done by the same examiners (NS, RM) at the University Hospital of Old Age Psychiatry and Psychotherapy at the University of Bern, Switzerland. On the first day of the experiment, we will test verbal intelligence [27], followed by an assessment of current mood (Profile of Mood States, POMS; Positive and Negative Affect Scale, PANAS) [28–30]. Then, the participants will put on a wearable device (Polar Verity Sense by Polar Electro Europe AG, polar.ch) on their left arm that will monitor their heart rate. Next, they will be asked about how many hours they had slept the night before and how awake and motivated they currently feel. Then, the attention network task and the prospective memory task will follow. Next, they will do a Go/No-Go task, a flexibility task, and a divided attention task (TAP) [31]. Finally, they will again rate their current mood and different naturalistic prospective memory tasks will follow. The second day of the experiment will be identical with the exceptions that we will apply stimulation for 20 min during the attention network task and the prospective memory task and that there will be no verbal intelligence test. At the end of the experiment, side effects, and the participants’ perception of the stimulation condition will be captured [32].

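### Session 1 is an unstimulated baseline, but the primary model treats it as a repeated outcome; this is valid, yet usually less precise than adjusting for it

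*Protocol article*

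**What the plan says.** All points are in the protocol article.

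- **Design (Study procedure).** The reason given for two sessions is: "All participants will be tested twice to differentiate learning effects from stimulation effects". On the stimulation itself: "The second day of the experiment will be identical with the exceptions that we will apply stimulation for 20 min". The caption of Fig 2 confirms that only the second assessment is stimulated. The attention tasks and the laboratory prospective memory task are given on both days, so each primary outcome has a session-1 value.
- **Allocation (Randomization).** "All participants will be randomly assigned to one of six experimental groups or the control condition". The expected session-1 means are therefore equal across the seven arms.
- **Primary model (Statistical analysis).** "We will use mixed ANOVAs or mixed effects models for statistical analysis of stimulation effects on primary outcome variables", the choice depending on missing data. The factors are then fixed: "We will use session (first, second) as within-subject factor and condition (six experimental groups or sham) as between-subject factor".
- **Covariates (Statistical analysis).** "We will include age as a covariate in all models". Control for mood or agitation is also planned. The session-1 score is nowhere named as a covariate, and nothing holds the session-1 means equal across arms.
- **Analysis set (Statistical analysis).** Only participants who came to both sessions are analysed, so requiring a session-1 score asks for no further attendance.

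**The concern.** A score taken before any stimulation in a randomised trial cannot be affected by the condition. Its use is to explain part of the person-to-person variation in session 2. Entering it as one level of the outcome, with a free mean per arm, forces the analysis to subtract the whole session-1 score. The stimulation contrast then carries the noise of both sessions, whereas covariate adjustment subtracts only the part of session 1 that predicts session 2.

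What is at stake is the width of the intervals and the power of the active-versus-sham comparisons, each of 15 against 15 participants, with multiplicity handled as "We will correct for multiple-comparisons using Bonferroni-Holm correction".

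**Working it through.** **The plan's own figures.** The article gives no figure for the precision of this contrast or for the between-session correlation, so there is none to reproduce on this point. Its one planning figure, a required n of 93 from η² = 0.32 with seven groups, does not reproduce as a one-way omnibus test at 0.05 (36 at 80% power, 52 at 95%; the power used is not stated). That is a separate matter, and nothing below rests on it.

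**Inputs.** Seven arms of 15, total 105 (Sample size calculation); two sessions, the first unstimulated (Study procedure); 0.05, taken as two-sided and unadjusted. Assumptions: rho from 0.3 to 0.9, and SD s1 in session 1 and s2 in session 2, at first both set to 1.

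**Step 1: what the planned model estimates.** With two sessions and both factors free, the session-by-condition contrast is the difference in mean change. On one simulated data set (rho 0.5), the mixed model gave an estimate of -0.186 with SE 0.3405, and an ANOVA on change scores gave the same two values. ANCOVA gave SE 0.3036, and the mixed model with equal session-1 means gave 0.302.

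**Step 2: residual variances.**
- Change: s1² + s2² - 2·rho·s1·s2, which is 2(1 - rho) when both SDs are 1.
- ANCOVA: s2²(1 - rho²), which is 1 - rho² when both SDs are 1.
- Difference: (s1 - rho·s2)², never negative. Apart from the small cost of estimating the slope, ANCOVA cannot be less precise.
- Ratio with equal SDs: (1 - rho²) / [2(1 - rho)] = (1 + rho)/2.

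**Step 3: size with equal SDs.** The detectable difference (80% power) is about (1.984 + 0.845) × residual SD × √(2/15), using 98 degrees of freedom for change. ANCOVA uses 97 and a small allowance for the slope. Example at rho 0.3: 2.83 × √1.40 × 0.365 = 1.22 for change, and 2.83 × √0.91 × 0.365 = 0.99 for ANCOVA.

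| rho | Variance, change | Variance, ANCOVA | Reduction | Detectable difference, change to ANCOVA (SD) |
|---|---|---|---|---|
| 0.3 | 1.40 | 0.91 | 35% | 1.22 to 0.99 |
| 0.5 | 1.00 | 0.75 | 25% | 1.03 to 0.90 |
| 0.7 | 0.60 | 0.51 | 15% | 0.80 to 0.74 |
| 0.8 | 0.40 | 0.36 | 10% | 0.65 to 0.62 |
| 0.9 | 0.20 | 0.19 | 5% | 0.46 to 0.45 |

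Below rho 0.5 the change variance exceeds 1, so the planned contrast is then less precise than ignoring session 1 altogether. Simulated variance ratios, change to ANCOVA, were 1.54, 1.29 and 1.15 at rho 0.3, 0.5 and 0.7, against 1.54, 1.33 and 1.18 in theory.

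**Step 4: unequal SDs.** With k = s2/s1 the ratio is (1 - rho²)k² / (1 + k² - 2·rho·k).
- rho 0.8, k 1.25: 0.5625/0.5625 = 1.00, no gain.
- rho 0.7, k 1.2: 0.7344/0.76 = 0.97, a gain of about 3% instead of 15%.
- rho 0.7, k 0.8: 0.3264/0.52 = 0.63, a gain of about 37%.

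The gain falls as k rises from 1 and is zero at k = 1/rho.

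**The case against.** **The planned analysis is legitimate.** This stands. A pre/post factorial in a randomised trial is unbiased. A reader might infer that the primary analysis is wrong or invalid; the documents do not support that. The point is one of efficiency.

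**Mixed models are already allowed.** The article could accommodate a model with a common session-1 mean, and such detail often sits in an analysis plan. As printed, however, both factors enter in full, and that gives the change contrast whichever of the two model types is used. Nor does the age covariate help: without a session interaction, a between-subject covariate cancels from the change contrast.

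**The session factor is there to separate learning from stimulation.** It does estimate practice directly, which an analysis of session 2 alone does not. But practice is common to all arms, including sham, so the comparison with sham still separates the two under ANCOVA. This is a reason to keep the factorial as a secondary description.

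**The size is uncertain.** This stands. Rho is not given, the gain is about 5% at rho 0.9, and equal SDs cannot be presumed when learning is expected and stimulation is applied in one session only.

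**Not every primary outcome is continuous.** This stands. False alarms, correct answers, missed targets and prospective memory accuracy are counts or proportions, and the article contemplates trial-level models, transformations and non-parametric alternatives. A reader might carry the table over to all primary outcomes; it applies to continuous ones only.

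**Two further readings go too far.** One is that the condition main effect would be tested, averaging in the unstimulated session and halving the effect; the article names no tested term. The other is that the trial is short of power because of this model. On the article's own η² of 0.32, one-way power at 93 is 99.96%; whether that effect size is credible is a different question.

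**Conclusion.** The point holds as an efficiency finding. The primary model leaves unused some of the information in a baseline that the trial collects anyway. Apart from the cost of estimating one slope, adjustment is never less precise, whatever the two SDs. How much it gains is conditional: a variance reduction of about 35% at rho 0.3 down to 5% at rho 0.9, for continuous outcomes with equal session SDs, less or nothing if session 2 is more variable, and more if it is less variable. The detectable differences are unadjusted, so after the Holm correction both analyses would need larger effects. Validity is not in question. The change is worth making because it costs almost nothing.

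**What to change.** - **Continuous primary outcomes** (the controlling variable and the reaction times): make the primary model the session-2 value on condition, with the session-1 value of the same outcome and age as covariates. Sex may be added, since it is a stratification factor. An equivalent choice is a mixed model with session-1 means constrained equal across arms, preferably with the two session variances left free.
- **Counts, accuracy and trial-level data:** use the corresponding generalised or generalised mixed model, with the session-1 score as covariate or a common session-1 level across arms.
- **Session-by-condition model:** keep it as a sensitivity analysis and to describe practice effects.

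Cost: a change of wording and one degree of freedom for the baseline (two if sex is added), with no new data. The article reports data acquisition as ongoing, with unblinding only at its end; if that is still so, the change should be recorded before unblinding. Otherwise it should be reported as a dated change.

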To answer these questions, we will systematically enhance or inhibit activity in frontal or parietal brain regions in healthy older adults during attentional control and prospective memory tasks. We will modulate activity in three areas; that is, the right superior parietal lobe, the right inferior frontal lobe or the left inferior frontal lobe. In order to replicate previous studies, we will test whether attentional control will predict laboratory prospective memory. In addition, we will test whether attentional control will also predict naturalistic prospective memory.

We hypothesize that the right inferior frontal gyrus and the right superior parietal lobe will be important for laboratory prospective memory as well as for attentional control. Modulation of the left inferior frontal cortex, however, will only lead to an improvement in prospective memory since attentional control seems particularly associated with the right hemisphere. Finally, we hypothesize that attentional control will predict laboratory prospective memory rather than self-reports or naturalistic prospective memory. Laboratory tasks share a similar setting and rely on timely motor responses while self-reports or naturalistic prospective memory tasks do not. To control for any effect of mood or agitation on cognition, we will examine current mood as well as the heart rate of all participants.

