### Sample size calculation

We used G*power [56] for the determination of sample size. Calculations were based on a previous non-invasive brain stimulation study in healthy young participants [22]. The effect size in this study (*η*² = 0.32) suggested a required sample size of n = 93 to detect robust effects in an ANOVA design with seven groups. We have increased the sample size to n = 15 in each group and will, therefore, include n = 105 healthy older individuals.

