## Discussion

In the current study, we will systematically enhance or inhibit activity in brain regions known to be associated with attentional control and prospective memory. This may contribute to our understanding whether more or less activity in these regions is associated with better attentional control or prospective memory in older healthy adults. We expect that enhancing activity in these brain regions will lead to more accurate and faster responses in laboratory prospective memory and attentional control tasks, due to increased excitability of underlying neurons. In contrast, we expect opposite effects when inhibiting activity. There is some evidence to suggest, though, that increasing the excitability of neurons does not necessarily lead to an increase in cognitive performance. Complex interactions between stimulation type, duration, stimulation strength as well as task characteristics or mood of the participants may play a role [57]. It could therefore be that inhibiting activity in a given region may actually increase task performance, due to an improved signal-to-noise ratio [58]. The theory behind that is that when a stimulus in the environment elicits activity in a brain region, stimulus-irrelevant noise is also present. The higher the signal in comparison to the noise, the more accurate the response of the participant. If stimulation does not enhance the signal-noise ratio but rather reduces it, performance may drop.

Besides performance improvement or worsening, it could also be that we will find differential effects on outcome measures. An increase in accuracy, for example, could be linked to slower responses, or reduced accuracy could be linked to faster responses. Since we will use different attentional control tasks and both laboratory and naturalistic prospective memory tasks, we will be able to disentangle these interactions and discuss possible implications.

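### The only stated model treats a polarity-by-region design as seven unordered groups, so its overall test does not answer the directional, region-specific question; contrasts within that model would

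*Protocol article*

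**What the plan says.** Under Randomization, the protocol article describes anodal or cathodal stimulation of the right inferior frontal, left inferior frontal or right superior parietal lobe, or sham. That is a 2 × 3 layout plus one control group.

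The expectations are directional and regional. The Introduction states: "We hypothesize that the right inferior frontal gyrus and the right superior parietal lobe will be important for laboratory prospective memory", and extends this to attentional control. For the left inferior frontal site it predicts an effect on prospective memory only. The Discussion expects better performance when activity is enhanced and continues: "In contrast, we expect opposite effects when inhibiting activity". It then allows that inhibition might improve performance in some region.

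Under Statistical analysis the model is: "We will use session (first, second) as within-subject factor", with "condition (six experimental groups or sham) as between-subject factor". The threshold is p "< 0.05 considered statistically significant", and the article adds: "We will correct for multiple-comparisons using Bonferroni-Holm correction". No polarity factor, region factor or contrast is named. The Sample size calculation also treats the design as a seven-group ANOVA: "We have increased the sample size to n = 15 in each group".

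**The concern.** An unordered seven-level factor ignores the structure of the arms. A significant session × condition test says only that the seven groups did not all change alike. It does not separate anodal from cathodal, or one region from another, and those are the questions posed in the Abstract and Introduction.

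It also spreads a structured signal over 6 df. If the follow-up is by pairs, each comparison uses 15 against 15, although the design offers 45 against 45 for polarity and 30 against 30 over the two right-sided sites. If contrasts are chosen only after the data are unblinded, directional claims become post hoc.

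**Working it through.** **Inputs from the article.** Seven groups of 15, N = 105; two sessions; α = 0.05 (taken as two-sided for contrasts). With two sessions, the session × condition test equals a one-way ANOVA on change scores, with 6 and 105 − 7 = 98 df. The age covariate takes away one df and hardly alters the results.

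**Assumed input.** Effects of ±d in SD units of the change score, with sham at 0. The article gives no such figure, so a range is shown.

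**The article's own figure.** "The effect size in this study (*η*² = 0.32") gives f² = 0.32/0.68 = 0.471. A seven-group ANOVA then needs N = 36 for 80% power, 44 for 90%, 52 for 95% and 67 for 99%. The stated 93 is not reproduced; that is a separate matter. At N = 105, λ = 105 × 0.471 = 49.4. The omnibus test has 99.99% power and a matching 1-df contrast more than 99.99%, so at this effect size the choice of test costs nothing.

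**Formulas.** Omnibus: λ = 15 × Σ(μ − mean μ)². Contrast with weights c: λ = (Σcμ)²/(Σc²/15). The joint 3-df test sums λ over the three within-region contrasts. Power comes from the noncentral F distribution.

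**Pattern A: ±0.3 SD at all three sites** (the prospective-memory expectation).
- Omnibus: λ = 15 × 6 × 0.09 = 8.1.
- Pooled anodal minus cathodal: λ = 0.6²/(2/45) = 8.1.
- One region: λ = 0.6²/(2/15) = 2.7. Joint test: λ = 3 × 2.7 = 8.1.

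**Pattern B: ±0.3 SD at the two right-sided sites, 0 at the left** (the attentional-control expectation).
- Omnibus: λ = 15 × 4 × 0.09 = 5.4.
- Pooled over three sites: mean difference 0.4, λ = 0.4²/(2/45) = 3.6.
- Two right-sided sites: λ = 0.6²/(2/30) = 5.4. Joint 3-df test: λ = 2 × 2.7 = 5.4.

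| Test | Pattern A | Pattern B |
|---|---|---|
| Omnibus, 6 df | 51% | 34% |
| Joint within-region, 3 df | 64% | 46% |
| Pooled over three sites, 1 df | 80% | 47% |
| Right-sided sites only, 1 df | – | 63% |

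For pattern A, omnibus against pooled contrast is 35% v 65% at ±0.25 SD and 66% v 91% at ±0.35 SD.

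**Single comparisons at ±0.3 SD.** Anodal against cathodal within one region has 37% power uncorrected, 22% at 0.05/3 and 7.6% at 0.05/21 (all 21 pairs). One active arm against sham has 13% uncorrected.

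**When the expected signs fail.** If one of the three regions reverses, the mean polarity difference falls to (0.6 + 0.6 − 0.6)/3 = 0.2, so λ = 0.2²/(2/45) = 0.9. The pooled contrast then has 16% power, while the omnibus keeps 51% and the joint test 64%, because neither depends on the sign within a region. If both polarities act equally in the same direction, every anodal-minus-cathodal contrast has λ = 0 and rejects only at the 5% level.

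**The case against.** A reader might infer that the plan cuts power from about 80% to about 50% for the very pattern it predicts. The article does not support that.

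- The 80% rests on an assumed ±0.3 SD, equivalent to η² of about 0.07, which appears nowhere in the article. At the one effect size it cites there is no loss.
- Equal effects at all three sites is not the prediction for attentional control, which supplies many of the primary outcomes. There the comparison is 34% v 47%.
- The article does not say that inference rests on the omnibus F. It sets out to determine whether enhancing or inhibiting each region changes the outcomes, and it foresees Holm-corrected comparisons. The seven-level factor is a saturated coding, so every contrast of interest can be estimated from it, and an analysis plan that is not shown may name them.
- The omnibus test does buy protection. The Discussion leaves the cathodal direction open, and with one reversed region the pooled contrast does far worse than the omnibus.

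All of this stands. It makes the power cost conditional and rules out leading with the pooled contrast. It does not remove the mismatch: the model and the sample size are both stated in terms of seven groups, while the hypotheses concern polarity and region. The Holm sentence names neither a family nor a contrast. The cited effect comes from young participants, and the Introduction says it is not fully understood whether such an effect carries over to older adults, so smaller effects are worth considering.

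**Conclusion.** The point holds as a mismatch between question and test, with a conditional cost. The stated 6-df test does not answer whether more or less activity helps in a given region. Under equal and opposite effects of ±0.3 SD, a joint within-region test gains about 13 percentage points over the omnibus at three responding sites (64% v 51%) and about 12 at two (46% v 34%). The best-matched 1-df contrast gains about 29 points in either case (80% v 51%; 63% v 34%). These figures assume full data on 15 per group and no correction across outcomes. They shrink to nothing as the effect approaches η² = 0.32. Low power for single regions comes from the group size, and no recoding of the factor will cure it.

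**What to change.** Keep the session × condition model and pre-specify within it:

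1. Anodal minus cathodal within each region, Holm-corrected over the three regions, with their joint 3-df test.
2. The polarity contrast pooled over regions and the polarity × region test (2 df); for attentional-control outcomes, also the contrast over the two right-sided sites.
3. Each active arm against sham, as supportive.
4. The seven-group omnibus test, retained.

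If an analysis plan already names such contrasts, align the article with it.

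The cost is analysis wording, with no new participants or assessments. The polarity contrasts are insensitive if both polarities act the same way, and the pooled contrast is also weak if one region reverses, so items 3 and 4 must stay. The plan should also state that single-region contrasts remain low in power: 37% uncorrected and 22% at 0.05/3, at ±0.3 SD.
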